#### a. Effectiveness

Continuous outcome measures will be used to measure the effectiveness of the present intervention. A t-test with intention-to-treat analysis will be performed. When missing data arises, methods like 'last observation carried forward' (LOCF) or 'multiple imputation' will be used. The central effect modifier with regard to the effect of collaborative care is comorbid chronic illness. Furthermore, somatoform presentation, associated symptoms of comorbid chronic illness, preference and adherence, life-events and social support, and personality traits will be included in the analysis as potential effect modifiers. The effect size will be estimated by Chi-square analysis and described in Cohen's d. Possible confounders, such as age, gender, immigrant status, level of education, and treatment history, will be included as variables in logistical regression analysis.

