### Randomisation

Patients in the participating departments who screened positive on the PHQ-9 and who have an MDD, according to the MINI, will be randomly allocated to the intervention group or the CAU group within their policlinic. Randomisation will be performed by the researcher, using a computerized method to avoid assignment bias. The patients will not be blinded for their group allocation.

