### Treatment of the patients in the control group

Half of the included patients function as a control group, in which they will receive CAU. The actual content of the CAU treatment (e.g. medication and number of contacts with physicians) will be assessed with the 'Scale assessing contacts between patients and practitioners' ('Contacten met dokters en andere behandelaars') and the 'Scale assessing medical utilization of health services' ('Vragenlijst medische consumptie') [57].

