#### 1. Primary outcome measure

##### Severity of depressive symptoms

The severity of the depressive symptoms is the primary outcome, and will be measured according to the depression sub-scale of the PHQ (PHQ-9). The PHQ-9 is a brief instrument that scores each DSM-IV criterion of a major depressive disorder on a scale ranging from zero (not at all) to three (nearly every day) [47]. The PHQ-9 has been found to be a valid and reliable instrument to measure the severity of depression in patients with different medical backgrounds [47]. In an earlier study, the PHQ-9 was used successfully for the diagnosis of MDD in diabetic patients [85].

An improvement of more than five points on the PHQ-9 can be considered a clinically relevant difference [86]. The PHQ-9 will be administered at baseline and during treatment at least every other week (before each appointment with the care manager). After treatment, the PHQ-9 will be administered every three months (3 (T_1_), 6 (T_2_), 9 (T_3_) and 12 (T_4_) months after baseline).

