### Power calculations

In this study, the PHQ-9 will be used as the primary outcome measure. In order to detect a standardised difference of 0.5 standard deviation in the primary outcome measure (which can be considered as a clinically relevant difference), 2 × 63 patients are needed when two-sided testing and 80% power is assumed. Intention-to-treat analysis will be applied. Therefore, 126 patients will be needed. An improvement of more than five points on the PHQ-9 can be considered a clinically relevant difference [86].

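### The primary t-test on PHQ-9 uses neither the baseline score as a covariate nor the clinic of randomisation: valid, but less efficient than the design allows

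*Protocol article*

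**What the plan says.** Under Analyses, a. Effectiveness, the only between-arm test described for the continuous outcome is this: "A t-test with intention-to-treat analysis will be performed". The same section gives examples of possible confounders (age, gender, immigrant status, education, treatment history) and assigns them to a logistic regression. Comorbid chronic illness appears there as the central effect modifier. No adjusted analysis of the continuous PHQ-9 is described.

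Two design features bear on this test. Under Randomisation, eligible patients "will be randomly allocated to the intervention group or the CAU group within their policlinic", and Recruitment of departments names three clinics: diabetes, cardiology and pulmonary. Under Severity of depressive symptoms, "The PHQ-9 will be administered at baseline and during treatment", so each patient has a baseline value of the primary outcome.

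Power calculations sizes the trial for an unadjusted comparison: "In order to detect a standardised difference of 0.5 standard deviation in the primary outcome measure", "2 × 63 patients are needed when two-sided testing and 80% power is assumed". It concludes "Therefore, 126 patients will be needed", with no addition for loss to follow-up.

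**The concern.** The baseline value of an outcome is usually its best single predictor, and clinic is the unit within which allocation is made. A test that uses neither leaves explainable variance in the error term. The trial is sized at 80% power with nothing in reserve, and outcomes are collected by mailed questionnaire over 12 months. At stake are some power, a wider confidence interval than necessary, and an estimate that carries part of any chance difference in baseline severity between arms of 63.

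**Working it through.** **Inputs from the article.** Effect 0.5 SD; 63 per arm; two-sided; 80% power; 1:1 allocation ("Half of the included patients function as a control group"); three clinics; PHQ-9 of at least 15 at entry.

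**Assumed, because the article does not give them.** Alpha 0.05; the baseline-outcome correlation r; the share c of outcome variance that lies between clinics.

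**1. The plan's own figure.** n per arm = 2(1.960 + 0.842)² / 0.5² = 62.8, rounded up to 63, so 126 in total. This reproduces the plan and supports alpha = 0.05. Power at 63 per arm is 80.1% by the normal approximation and 79.5% by the noncentral t.

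**2. Adjusting for baseline.** The residual variance becomes 1 − r², so the effective standardised difference is 0.5/√(1 − r²). Adding clinic makes the residual variance 1 − r² − c. Power by the noncentral t, 63 per arm:

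| r | 1 − r² | effective d | power, baseline only | power, baseline and clinic, c = 0.05 |
|---|---|---|---|---|
| 0 (t-test) | 1.00 | 0.500 | 79.5% | – |
| 0.1 | 0.99 | 0.503 | 79.9% | 81.9% |
| 0.2 | 0.96 | 0.510 | 81.1% | 83.1% |
| 0.3 | 0.91 | 0.524 | 83.1% | 85.1% |
| 0.4 | 0.84 | 0.546 | 86.0% | 88.0% |
| 0.5 | 0.75 | 0.577 | 89.5% | 91.4% |

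Clinic therefore adds about 2 points at c = 0.05, and under 1 point at c = 0.02.

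Simulation (three clinics of 42, exact balance within clinic, 6,000 runs) agrees. At r = 0.3, c = 0.05 the t-test has 80.0% power and the adjusted model 84.6%. At r = 0.5, c = 0.05 the figures are 80.8% and 91.3%. When neither covariate predicts anything they are 80.5% and 80.3%, so adjusting for useless covariates costs almost nothing.

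**3. If the t-test is on change scores.** The article does not say. Let k be the baseline SD divided by the follow-up SD. The change-score variance is 1 + k² − 2kr, and it exceeds the ANCOVA variance by (1 + k² − 2kr) − (1 − r²) = (k − r)², which is never negative. A change-score test is therefore never more efficient than ANCOVA. With equal SDs (k = 1) its power by the normal approximation is 66.0% at r = 0.3 and 80.1% at r = 0.5, against 83.7% and 90.0% for ANCOVA. The entry cut-off may make k less than 1, which narrows the gap but cannot reverse it.

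**4. Type I error of the t-test.** Suppose allocation is exactly balanced within clinic. The true variance of the difference is then smaller by the factor 1 − c, while the t-test still counts c as error. The large-sample rejection rate is P(|Z| > 1.96/√(1 − c)). For c = 0.06 this is P(|Z| > 2.022) = 4.3%; simulation gave 4.1% to 4.2%. For c = 0.02 it is 4.8% (simulated 4.6%). With simple allocation within clinic and c = 0.06 the simulated rate was 5.0%.

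**5. Chance baseline imbalance.** The standard error of the baseline difference is √(2/63) = 0.178 SD, so the 95% range is ±1.96 × 0.178 = ±0.35 SD. An unadjusted follow-up comparison shifts by r times the imbalance. At the edge of that range the shift is 0.3 × 0.35 = 0.10 SD at r = 0.3 and 0.5 × 0.35 = 0.17 SD at r = 0.5, or about 21% and 35% of the 0.5 SD target. The typical (one standard error) shift at r = 0.3 is 0.3 × 0.178 = 0.05 SD.

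**The case against.** The strongest reply is that nothing here is wrong. A t-test is a valid comparison of randomised arms, the sample size was calculated for it, and covariate detail is often left to an analysis plan, which is not shown. The first two points stand in full. The third stands only in part: the article does not stay silent but names a specific unadjusted test.

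Three stronger readings are tempting, and the article does not support them.

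- **The t-test's standard error is too large after within-clinic randomisation.** A reader might infer this from the Randomisation section. That section mentions only a computerised method within clinic, without blocks or any other balancing device. Simple randomisation within clinics leaves the t-test correctly calibrated. The test is conservative only if allocation is balanced within clinic and clinics also differ materially.
- **Baseline imbalance biases the result.** Imbalance enters in proportion to the baseline-outcome correlation, and the t-test's standard error already allows for it.
- **The plan excludes baseline and clinic from all adjustment.** The confounder list is given as examples. Chronic illness, which largely tracks clinic because each clinic recruits its own index disease, is analysed as an effect modifier. Neither of these alters the t-test itself.

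It is also fair to object that the gain may be small. The cut-off of 15 restricts the baseline range and probably lowers r. At r = 0.1 to 0.2 the gain from baseline is only 0.4 to 1.6 points.

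**Conclusion.** The point holds as a matter of efficiency. The stated t-test is valid and 126 patients is correct for it, but a linear model using data the trial already collects would do at least as well under any reading of that test, apart from a negligible cost in degrees of freedom. The gain from baseline runs from under 1 point of power at r = 0.1 to 10 points at r = 0.5. Clinic adds up to about 2 points at 5% of outcome variance. All of this rests on assumed values of r and c, and the lower values of r deserve weight. The t-test's slight conservatism (type I error about 4%) is conditional on balanced allocation within clinic and on an assumed clinic share of about 6%. The change is worth making because it costs almost nothing and the sample size has no reserve. Under an assumed 20% loss, normal-approximation power is 70.9% for the t-test, against 74.9% at r = 0.3 and 82.6% at r = 0.5 with baseline adjustment.

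**What to change.** In Analyses, a. Effectiveness, make the primary analysis a linear model of PHQ-9 on arm, baseline PHQ-9 and clinic (three levels). This can be ANCOVA at the primary time point or a mixed model over T1 to T4 with the treatment contrast at that time point. Report the t-test as a sensitivity analysis, and state whether it uses follow-up or change scores. Keep 126 patients and treat any gain as a buffer against loss to follow-up, not as a reason to recruit fewer.

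The cost is analysis wording only. Both covariates are already recorded, and no patient, visit or questionnaire is added. The change should be made before outcome data by arm are seen.

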### Recruitment of departments

The study has been set up in co-operation with the Onze Lieve Vrouwe Gasthuis (OLVG) in Amsterdam. The diabetes, cardiological, and pulmonary outpatient clinics of the OLVG will participate in the study.

A psychiatrist will be trained to provide the collaborative care intervention, together with a care manager. He will receive training in contracting (together with the care manager) and the antidepressant algorithm.

Consultative psychiatric nurses will be trained to provide the collaborative care intervention in the role of care manager. They will receive training in monitoring, care-management, PST, and contracting. The department nurses will receive training in screening for depressive disorder. The care managers in the intervention group will be closely monitored by the research team, in order to ensure that the intervention is provided correctly. There will be no care manager for patients receiving CAU.

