For patients who are assigned to the intervention group a consultation will be arranged, first with the care manager and then with a psychiatrist, to provide more information about the treatment and to formulate a treatment plan together (contracting). Patients assigned to the CAU group will be told that they can consult their general practitioner if they feel that they need treatment, and they will be monitored (see Figure 2 for a schematic diagram). Patients will only be included in the study after they have given written informed consent. The Medical Ethical Committee of the Onze Lieve Vrouwe Gasthuis has approved the trial (study no WO06-066).

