#### Ad a) Contracting

The care manager and the consultant psychiatrist in the hospital together inform the patient that the diagnosis is a depressive disorder. The patient will receive psycho-education about the course and the treatment options, and is offered the choice of evidence and guideline-based treatments. Depending on the patient's preferences, a joint treatment contract is formulated by the psychiatrist, the care manager and the patient. The aim of the contract is to make clear that the treatment arrangements must be adhered to by all parties involved. In an earlier study in the Netherlands, based on a collaborative care model, collaboration was indeed enhanced by contracting [55].

During the intervention phase, the patient is asked to fill in the PHQ-9 ahead of every appointment in order to evaluate the progress. The treatment steps are evaluated with the care manager. If a patient is not satisfied with the chosen treatment, (s)he can change to another form of treatment, and this will be confirmed in a new contract. If a patient wishes to withdraw from the intervention, (s)he will continue to receive CAU. All treatment choices are well documented as process measures.

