The second section of the TiC-P includes a short form of the Health and Labour questionnaire (HLQ) for collecting data on productivity losses [107]. The Short-Form HLQ (SF-HLQ) consists of three modules that measure productivity losses: absence from work, reduced efficiency at work and difficulties with job performance [108]. The number of days absent from work and the actual cost of hours missed at work due to health-related problems are valued according to the average value added per worker by age and gender per day and per hour, respectively. If respondents indicate that they have been absent for the entire recall period, data will be collected from the time when the period of long-term absence started. This additional information will be used to value the production losses according to the friction cost method [109,110]. The friction cost method takes into account the economic circumstances that limit the losses of productivity to society, which are related to the fact that a formerly unemployed person may replace a person who becomes disabled [109].

For the economic evaluation, the effects will be measured according to utility scores. In addition to the clinical outcome parameters, the utility scores will supply additional information about the impact of collaborative care on the treatment of MDD compared to the impact of CAU on the general health related quality of life. Furthermore, the results can be compared to a broad range of other health care interventions, also outside the field of mental health care.

The cost-utility will be evaluated by relating the difference in direct medical costs per patient receiving collaborative care or CAU to the difference in terms of QALYs gained, which yields a cost per QALY estimate. Furthermore, we will also estimate the cost per QALY, including the productivity costs.

In the case of missing data on costs and/or effects, and the additional uncertainty this introduces, we will use 'multiple imputation' [111]. We will use the Monte Carlo Markov Chain (MCMC) approach to impute the missing values. The uncertainty will be assessed with bootstrapping, and the results will be presented in acceptability curves [112].

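### The primary PHQ-9 analysis may use last observation carried forward, which biases the arm comparison when missingness differs between unblinded arms; the plan should fix one better method on the mailed T0-T4 scores.

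*Protocol article*

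**What the plan says.** The Effectiveness subsection of the Analyses fixes the test, "A t-test with intention-to-treat analysis will be performed", and then the handling of gaps: "When missing data arises, methods like 'last observation carried forward' (LOCF) or 'multiple imputation' will be used". Neither method is made primary.

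Outcome questionnaires go by mail to both arms at baseline, 3, 6, 9 and 12 months (Data collection). The section on the primary outcome adds a second set of scores: "The PHQ-9 will be administered at baseline and during treatment at least every other week (before each appointment with the care manager". The contracting section describes the same forms: "the patient is asked to fill in the PHQ-9 ahead of every appointment in order to evaluate the progress". Only the intervention arm has these appointments, because "There will be no care manager for patients receiving CAU". Usual-care patients are told they can see their general practitioner, "and they will be monitored", but no instrument or interval is given for that monitoring.

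The economic section chooses multiple imputation alone, with a sentence that begins "In the case of missing data on costs and/or effects, and the additional uncertainty this introduces". The effects there are utility scores.

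**The concern.** Selection on a PHQ-9 of at least 15 makes a later fall likely in both arms, from natural course and regression to the mean as well as from treatment. Carrying an earlier score forward therefore puts missing patients too high. If both arms lose the same share of patients at the same times and follow the same course, the errors cancel in the difference. If not, they remain. Patients and nurses know the allocation, and only one arm has regular contact with a care manager, so unequal return of questionnaires is plausible. The t-test also counts each carried value as a measurement, so the uncertainty about it disappears.

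A second route is possible. If the fortnightly clinic forms counted as observations, a control patient without a T1 form could carry only the baseline score, while an intervention patient could carry a recent, improved one. That would favour the intervention even with equal dropout and no true effect.

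At stake is the primary result: a difference between arms produced by the handling of missing data.

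**Working it through.** **The plan's own figure.** For 0.5 SD, two-sided, 80% power and an assumed 5% level (the article states none), n = 2 × (1.96 + 0.842)² / 0.5² = 62.8, so 63 per arm. The stated 2 × 63 = 126 is reproduced and is used below.

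**Inputs.** From the article: 63 per arm, t-test, entry at PHQ-9 of 15 or more, first common follow-up at 3 months (T1). Not in the article, hence assumed: the share missing at T1, the PHQ-9 SD and the improvement under usual care. All cases have no true effect and the same mean course in both arms. Bias is intervention minus control, so a negative value looks like benefit.

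**A. Mailed T0-T4 forms only.** A patient missing T1 carries baseline in either arm, so bias = improvement × (share missing in intervention − share missing in control).

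- Equal missingness: improvement × 0 = 0. Simulations with 10% to 40% missing gave differences within 0.04 points and 4.4% to 5.8% false positives, which is noise around 5%.
- 10% intervention, 25% control: 3 × (−0.15) = −0.45; 5 × (−0.15) = −0.75; 7 × (−0.15) = −1.05. The simulation (baseline SD 3, T1 SD 5.5, correlation 0.4, 3,000 runs) gave −0.46, −0.75 and −1.05, with 7.6%, 12.7% and 16.7% false positives. A longer run of 20,000 gave 7.6%, 12.0% and 17.6%.
- Reversed, 25% intervention and 10% control: +0.45, +0.75 and +1.05. The sign follows the arm that loses more patients.

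**B. Clinic forms also carried forward (a possible reading only).** With equal missingness, bias = −(share missing) × (improvement) × (fraction of the improvement reached at the last clinic form). For 20% missing and 5 points:

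| Fraction reached at last form | Formula | Simulated bias | False positives |
|---|---|---|---|
| Last form spread evenly over weeks 0 to 10, linear course: mean fraction 5/12 = 0.42 | 0.20 × 5 × 0.42 = 0.42 | −0.41 to −0.42 | 6.6% to 7.1% |
| Same spread, early improvement: mean fraction 0.63 | 0.20 × 5 × 0.63 = 0.63 | −0.66 | 10.8% |
| 80% of the change already reached | 0.20 × 5 × 0.80 = 0.80 | −0.78 to −0.80 | about 13% |

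The first two rows use SD 5 and the third a T1 SD of 5.5. In SD units the first and last rows are 0.42/5 = 0.08 and 0.80/5.5 = 0.15, against the planned 0.5.

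Under the linear, spread-out course with 5 points, the bias is 0.20 points (5.4%) at 10% missing and 0.85 points (14.1%) at 40%.

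**C. Later visits, clinic forms included.** With SD 5, a 5-point linear fall to T1 and none after, and 20% dropout spread evenly over follow-up, the bias is −0.42 (6.6%) at T1, −0.20 (5.8%) at 6 months and −0.09 (4.0%, nominal within noise) at 12 months. Treatment lasts at most 22 weeks, after which there are no new clinic forms, and controls have later mailed scores to carry.

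**The case against.** A reader might infer that the plan carries the clinic forms forward and so builds in a benefit for the intervention. The article does not say so, and much of it points the other way. The contracting section gives the forms' purpose as checking progress, and the antidepressant section uses the PHQ-9 to guide treatment steps. Data collection and Outcome parameters describe mailed T0-T4 measurements in both arms. Outcomes are to be measured by a blinded research assistant, and survey results are withheld from hospital staff, whereas the care manager necessarily works with the clinic forms. This stands. What remains is an ambiguity: the primary-outcome section lists the fortnightly forms without excluding them.

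It also stands that the figures depend on assumptions, that 0.8 points needs most of the improvement to have occurred before the last form, and that T1 is the worst visit, while the article names no single primary time point. Under unequal dropout with mailed forms only, the bias can go either way, so it cannot be said always to favour the intervention.

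Nor does the economic section already set up imputation of PHQ-9 scores; it covers costs and utilities.

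Finally, a condensed article may leave the choice of method to an analysis plan, and multiple imputation is already one of the named options. Leaving details open would be no finding. But LOCF is named as acceptable for the primary analysis, and that is a stated choice which can be improved.

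**Conclusion.** The concern holds in limited form. LOCF is a poor permitted choice for the primary outcome: it treats carried scores as data, and when scores fall over time it biases the comparison if the amount or timing of missingness differs between arms. With the mailed forms alone and no true effect, the bias at T1 is nil under equal missingness and about 0.5 to 1.0 points, with 8% to 17% false positives, at an assumed 10% versus 25% missing and 3 to 7 points of improvement.

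The clinic-form route is a further risk, conditional on a reading that the article neither adopts nor rules out. At T1, with an assumed 20% missing in both arms and 5 points of improvement, it is worth about 0.4 points (7%) if dropout is spread over treatment and about 0.8 points (13%) if 80% of the change is complete. It shrinks at later visits, and would reverse if scores worsened.

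Dropout, SD and usual-care course are all assumed, so these figures show possible size and are not forecasts. This should be fixed before analysis; it does not by itself invalidate the trial.

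**What to change.** Three changes to the Effectiveness subsection:

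1. Remove LOCF as an option for the primary analysis.
2. Name one primary approach: either multiple imputation, done separately by arm, on the mailed T0-T4 PHQ-9 scores, or a likelihood-based repeated-measures model on the same scores. The first keeps the planned t-test and matches the type of method chosen for costs and utilities, though the PHQ-9 imputation model still has to be written.
3. State that PHQ-9 forms completed for care-manager appointments are not used to fill study visits.

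A sensitivity analysis under missing-not-at-random assumptions would be a useful addition but is optional.

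The cost is a few sentences and modest analysis work. Sample size, data collection and conduct do not change.

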### Treatment of patients in the intervention group

In the *collaborative care framework *used in this study, active collaboration of the patient with the treatment is enhanced. The care is tailored to the patient's needs within an active team, which consists of the patient, the care manager and the consulting psychiatrist. If the care manager experiences difficulties in this process, (s)he can consult the psychiatrist. Within the team the need for and assessment of the required treatment will be determined, and a treatment plan will be formulated. Subsequently, the care managers will co-ordinate the care and evaluate each step, together with the patient. According to the stepped care principle, treatment response will be monitored once every two weeks [54]. If necessary, each treatment step will be followed by a subsequent step to improve the outcome. For patients who solely receive PST, this subsequent step can involve six extra sessions of PST and/or adding antidepressant medication (AD), or switching to antidepressant medication only. The same method will be applied to patients who are treated with both PST and antidepressant medication.

The framework also includes *patient and provider adherence-improving techniques*. Provider adherence-improving interventions are administered by the research group. Provider adherence has been enhanced in an earlier study in primary care, in which psychiatrists instructed general practitioners by means of consultations, combined with phone calls and written instructions that were distributed regularly [55]. Such an approach was also found to be feasible and effective in the USA [56]. In the present study, the adherence of care managers will be improved in a similar way. Patient adherence will be improved by contracting and psycho-education [55,57].

In the present setting, the collaborative care framework includes four treatment options superimposed on adherence-enhancing techniques. The patients will have the choice of receiving antidepressant medication, but PST, contracting and manual-guided self-help are obligatory.

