#### 4. Additional outcome measures and effect modifiers

*Depressive symptoms *will also be assessed with the 'Inventory for Depressive Symptomatology-Self Report' (IDS-SR) [81]. Remission (i.e. reduction in DSM-IV criteria below the threshold for a diagnosis of depressive disorder [68]) of depressive symptoms will be measured according to the PHQ-9. Remission on the PHQ-9 is defined as a score of five or below [86].

*Somatoform presentation *will be assessed with five questionnaires. Firstly, presentation will be assessed as the number and intensity of functional somatic complaints a patient reports on the 'Bodily Complaints Questionnaire' ('Lichamelijke Klachten Vragenlijst' [LKV]) [93]. Secondly, possible comorbid somatoform disorder will be assessed with the 'Screening for Somatoform Symptoms – 7' (SOMS-7) [94]. Thirdly, hypochondria will be measured with the 'Whitley Index' (WI) [95,96]. Fourthly, health anxiety and illness behaviour will be measured with the 'Illness Attitude Scale' (IAS) [95]. Finally, pain will be measured with one scale of the SF-36 and a visual analogue scale (VAS).

*Associated symptoms of comorbid chronic illness *will be measured as fatigue, according to the Dutch version of the 'Multidimensional Fatigue Inventory' ('Multidimensionele Vermoeidheids Index' [MVI-20]) [97,98] and as disability with the 'World Health Organization-Disability Assessment Survey-II' (WHO-DAS-II) [99].

*Preference and adherence*. Preferences of the patient will be assessed according to the choices patients make in the intervention group. Patient and provider adherence will be assessed by means of a qualitative questionnaire [57]. The working relationship between the patient and the care manager will be measured with the 'Helping Alliance Questionnaire' (HAQ-II) [100], because the care manager will provide PST [101]. The attitude of the care manager towards the treatment of depressive disorder will be measured with the Depression Attitude Questionnaire (DAQ) [102,103]

*Life-events and social support *will be assessed according to the 'Social Readjustment Rating Scale' [104] to indicate the amount of change in daily life, and by two items on the SF-36 [90].

*Personality traits *will be measured according to the neuroticism and extraversion scales of the 'NEO Five-Factor Inventory' (NEO-FFI), the abbreviated version of the NEO personality inventory [105].

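### Preference is measured only in the intervention arm and adherence arises after randomisation, so neither can serve as an effect modifier of collaborative care versus CAU

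*Protocol article*

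**What the plan says.** The protocol section Analyses, a. Effectiveness, names comorbid chronic illness as the central modifier of the effect of collaborative care. It then adds further domains: "preference and adherence, life-events and social support, and personality traits will be included in the analysis as potential effect modifiers". The effect to be modified is therefore the contrast between collaborative care and CAU.

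The section 4. Additional outcome measures and effect modifiers says how these variables are obtained:

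- Preference: "Preferences of the patient will be assessed according to the choices patients make in the intervention group".
- Adherence: "Patient and provider adherence will be assessed by means of a qualitative questionnaire". Neither the arm nor the time point is given.
- Two measures under the same heading depend on the care manager. One is the alliance score ("The working relationship between the patient and the care manager will be measured with the 'Helping Alliance Questionnaire"); the other is the care manager's own attitude towards treating depression.

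Four statements elsewhere bear on these variables:

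- Recruitment of patients places the treatment-planning contact after assignment: "For patients who are assigned to the intervention group a consultation will be arranged, first with the care manager and then with a psychiatrist".
- Ad a) Contracting lets a patient switch treatment later and adds: "All treatment choices are well documented as process measures".
- Treatment of patients in the intervention group: "Patient adherence will be improved by contracting and psycho-education".
- Recruitment of departments: "There will be no care manager for patients receiving CAU".

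**The concern.** Estimating effect modification in a two-arm trial requires comparing the treatment effect across levels of a variable. Each level must therefore contain randomised patients from both arms, and the variable must not itself be a result of treatment. Baseline characteristics satisfy this. Preference as measured here does not, because it has no control-arm values. Adherence does not, because it follows allocation and is something the intervention is designed to raise.

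What is at stake is a secondary conclusion. An analyst who follows the list literally finds that the preference interaction has no estimate. A natural substitute is to split the intervention patients by adherence or choice and set each part against the whole control group. That comparison is no longer protected by randomisation. Patients who adhere may have a better prognosis anyway, and the difference would be credited to treatment. The report could then say that collaborative care works in adherent patients when the data show no such thing.

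**Working it through.** **1. The plan's own target, as a yardstick.** Power calculations gives a 0.5 SD difference, two-sided testing, 80% power and 63 patients per arm. Alpha is not stated; 0.05 is assumed. Per arm, n = 2 × (1.960 + 0.842)² / 0.5² = 62.8, rounded up to 63, so 126 in total. The stated figure is reproduced and is not in dispute.

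**2. Can an arm-by-preference interaction be estimated?** Let T = 1 for collaborative care and 0 for CAU, and let M be preference. The usual model is

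E(Y) = b0 + b1·T + b2·M + b3·T·M.

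M is observed only when T = 1. Suppose controls are given a placeholder value c. Then M = c·(1 − T) + T·M, so the column for M is a linear combination of the columns for the constant, T and T·M. With c = 0 the columns M and T·M are identical. A design matrix with 63 patients per arm and M present only in the intervention arm has rank 3 for 4 coefficients, so b2 and b3 cannot be separated. The data give only the association of preference with outcome inside the intervention arm. That mixes prognosis with any modification, and a larger sample does not help. With a binary M observed in both arms the same matrix has rank 4 of 4, so the obstacle is how preference is measured, not the model.

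The alliance score and the care-manager attitude score, if entered as modifiers, have the same structure: without a care manager under CAU, there is no control value.

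**3. Patient adherence.** Here the text leaves two possibilities.

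- Only intervention patients answer the questionnaire. Step 2 then applies.
- Both arms answer. The matrix may have full rank, but adherence to CAU and adherence to the collaborative care package concern different regimens. Both arise after allocation, and the intervention acts on the second. Patients at the same adherence level in the two arms are not comparable by randomisation.

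Neither possibility gives a valid pre-treatment modifier.

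**4. Size of the bias in the substitute comparison.** Assume no treatment effect, an adherence score and outcome that are jointly normal with correlation r, and a median split in the intervention arm. The mean of the upper half of a standard normal is √(2/π) = 0.798. The more adherent half then appears better than all controls by 0.798 × r, and the less adherent half worse by the same amount.

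| Assumed r | More adherent half vs all controls | Gap between halves (2 × 0.798 × r) |
|---|---|---|
| 0.1 | 0.08 SD | 0.16 SD |
| 0.3 | 0.24 SD | 0.48 SD |
| 0.5 | 0.40 SD | 0.80 SD |

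A null simulation (4,000 trials, 63 per arm) agrees. It let one prognostic factor drive both the outcome (assumed loading 0.5) and adherence (that factor plus equal-variance noise). The implied r is 0.5/√2 = 0.354, for which the formula gives 0.798 × 0.354 = 0.28 SD. The simulation gave 0.28 SD better for adherers, 0.28 SD worse for non-adherers, and a gap of 0.57 SD.

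The protocol gives no value for r, so this range is illustrative.

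**The case against.** A reader might infer that adherence, like preference, exists only in the intervention arm. The protocol does not support that for patient adherence. It names a questionnaire but neither the arm nor the time point. CAU patients may consult their general practitioner, and their medication and contacts are recorded, so a control-arm measure is not ruled out. The secure objection to patient adherence is its timing after randomisation, not its absence in one arm.

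A reader might also infer that the protocol plans to compare adherers with all controls. It describes no such comparison, and within-arm analyses are also possible. The figures in step 4 show what would follow if that route were taken.

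The Effectiveness section does not name the alliance score, and the section that defines it covers outcome measures as well as modifiers. It may have been meant as a process measure only, so the point about care-manager measures is conditional.

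It is tempting to go further and fault the other listed modifiers for not being tied to baseline, or the list for lacking a multiplicity rule. A baseline measurement is planned, and both details are commonly left to a statistical analysis plan, which is not shown here. Neither is a finding.

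Finally, these variables are called only potential modifiers, and no primary conclusion rests on them. That limits the consequence. It does not make the stated analysis feasible: the protocol assigns these variables a role that its own measurement description rules out for preference and its own treatment description rules out for adherence.

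**Conclusion.** The point holds in a limited form and should be corrected. For preference it follows from the text alone: choices are observed only in the intervention group, after allocation, so the arm-by-preference interaction is not estimable. For the care-manager measures the same is true if they are used as modifiers. For patient adherence, whichever arm is asked, it is behaviour after randomisation that the intervention targets, and so is not a valid pre-treatment modifier.

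The possible bias, if intervention patients were split by adherence and compared with all controls, is 0.08 to 0.40 SD for r between 0.1 and 0.5, against a design target of 0.5 SD. This assumes no true effect, joint normality and a median split; r is not from the protocol.

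A reader might conclude that the main result is compromised. It is not: the intention-to-treat t-test on the PHQ-9, the sample size of 126 and the cost-utility analysis do not use these variables.

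**What to change.** In Analyses, a. Effectiveness, remove preference and adherence, with the care-manager measures under that heading, from the list of potential effect modifiers. State instead that they will be reported as process measures or examined as predictors of outcome within the intervention arm, and that such associations are not causal. This agrees with the contracting section, which already treats the choices as process measures. Comorbid chronic illness stays as the central modifier, and the other listed domains are untouched.

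The cost is a change of wording. No data collection changes, and no valid estimate of effect modification is lost.

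If modification by preference is itself of interest, preference would have to be asked of all patients before randomisation. The sponsor should then expect little power. With an even split (assumed) and 126 patients, the interaction has standard error √(4/31.5) = 0.356 SD. Power to detect a 0.5 SD interaction at two-sided 0.05 is then Φ(0.5/0.356 − 1.960), or about 29%.
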